### Primary end points

We identified two primary end points, one defined by a combination of clinical parameters related to specific functional deficits experienced by patients with MS and the other one based on MRI findings, both measured 12 months after randomization.

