#### Patients with RRMS

The sample size was estimated on the basis of the primary end point on MRI. We assume that the average total number of MRI active lesions in the control group is equal to 6 with a standard deviation of 7.6
[53]. The intention-to-treat (ITT) analysis of 423 patients, allocated into the two treatment arms according to a randomization ratio of 1:2 (141 in the control arm and 282 in the experimental arm), will allow us to detect an absolute mean reduction of 2.1 lesions with an α error of 0.05 (two-sided likelihood ratio test (LRT)) and a power of 90% (power analysis based on 5,000 simulations, assuming a negative binomial distribution). Thus, we will be able to highlight a 1-year mean reduction from 6 lesions in the control arm to 3.9 in the experimental arm, which corresponds to a relative reduction of 35%. Even in the presence of a higher level of variability, with a standard deviation of nine lesions, our study would have a power of 81%, to show as statistically significant the same difference. This sample size will also be able to show a reduction of at least 0.3 in the annualized relapse rate with a power greater than 93%, (0.6 vs. 0.9 in the control arm, α = 0.05, two-sided LRT). The sample size of 423 patients is also adequate for the evaluation of the combined clinical end point with a 92% power or higher to detect a 15% increase in the percentage of improved patients (with a 5% to 15% figure in the control arm, α=0.05, two-sided test on proportions). To obtain a sample size of 423, a total of 445 patients will be recruited (148 in the control arm and 297 in the experimental arm), to take into account a 5% dropout rate, leading to nonevaluation of the primary end point at 12 months.

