[58,59]. For this reason, two primary end points were identified, one defined by a set of clinical instrumental parameters related to specific functional deficits experienced by patients with MS and the other one based on MRI findings, both measured 12 months after randomization. The decision to utilize two primary end points emerged from various considerations. First, the hypothesized effect of angioplasty for MS patients with CCSVI does not allow exclusion of a clinical effect independent of the incidence of active MRI lesions. On the other hand, MRI parameters are largely utilized as indicators of activity in clinical trials for MS and are considered robust with respect to any placebo effect. The observation of a statistically significant advantage in only one of the two end points (clinical or MRI) will be sufficient to declare the study results in favor of the superiority of angioplasty over sham procedure. In the event of conflicting results (active treatment favored by one end point and not favored by the other one), the combined clinical end point will prevail. Second, the use of two primary end points in this situation offers at least two advantages: (1) If masking of both participants and investigators succeeds, the demonstration of a significant effect of the treatment on even only one of the two end points would be sufficient to reject the hypothesis that venous angioplasty is not active or efficacious in patients with MS; and (2) in the event that failure of the masking occurs, thus potentially weakening the evidence coming from the clinical end point, the evaluation of the MRI end point would maintain its validity entirely, thereby permitting the study to conserve, even if only partially, scientific and clinical usefulness.

A novel functional composite end point was defined to assess the primary clinical end point. The reason for this decision was that the EDSS

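### Two adjacent decision rules give different verdicts when MRI favours angioplasty and the clinical end point does not, because the term that would separate them is undefined

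*Protocol article*

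**What the plan says.** The Primary end points section names two: "We identified two primary end points, one defined by a combination of clinical parameters", and a second based on MRI. Both are measured at 12 months.

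The rule for combining them stands in the Discussion, in the paragraph that explains why there are two:

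- **Rule 1.** "The observation of a statistically significant advantage in only one of the two end points (clinical or MRI) will be sufficient to declare" superiority of angioplasty over sham.
- **Rule 2**, the next sentence. Where results conflict ("active treatment favored by one end point and not favored by the other one), the combined clinical end point will prevail").
- **Rule 1 again**, a few lines later, on the condition that masking succeeds: "demonstration of a significant effect of the treatment on even only one of the two end points would be sufficient to reject the hypothesis" that angioplasty is inactive.
- **The case of failed masking.** The clinical evidence may be weakened, but "the evaluation of the MRI end point would maintain its validity entirely".

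The Statistical analyses section tests each end point at a two-sided 5% level and gives no combining rule. The article does not define *favored*, *not favored* or *conflicting*, and does not say which rule yields to the other.

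**The concern.** A win on one end point only is the case that Rule 1 is written for, and it names MRI as one of the two end points that may supply the win. Rule 2 describes its own case in words that also fit a win on one end point only. If that win is on the clinical end point, the rules agree. If it is on MRI, Rule 1 declares superiority, and Rule 2 passes the verdict to a clinical result that does not support it.

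The outcome matters because the RRMS sample size was set on the MRI end point, and because the Discussion itself allows that clinical and MRI effects may diverge. If the text is left as it is, the meaning of *not favored* can be chosen after the results are known, and the same data could be reported as a positive or a negative trial with the protocol cited for either.

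**Working it through.** **1. Where the rules differ.** Take each end point as significantly better, not significant, or significantly worse with angioplasty.

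| Clinical | MRI | Rule 1 | Rule 2 |
|---|---|---|---|
| better | better | superiority | not engaged |
| better | not significant or worse | superiority | superiority (clinical prevails, if engaged) |
| not significant | better | superiority | no superiority, if *not favored* includes a non-significant result |
| worse | better | superiority | no superiority on any reading |
| not better | not better | none | none |

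The rules part only when MRI wins and the clinical end point does not. How much of that outcome Rule 2 takes over depends on the undefined term.

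**2. The plan's own figures (Sample size, Patients with RRMS).** The plan assumes 141 control and 282 experimental patients, "average total number of MRI active lesions in the control group is equal to 6 with a standard deviation of 7.6", a fall to 3.9 lesions, and "α error of 0.05 (two-sided likelihood ratio test (LRT)) and a power of 90" percent. A negative binomial model with common dispersion has k = mean² / (SD² − mean) = 36 / (57.76 − 6) = 0.696. A simulation of the likelihood ratio test (2,000 runs) gives:

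- SD 7.6: power 0.906 (stated 0.90)
- SD 9: power 0.796 (stated 0.81)

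For the clinical end point, a 15-point increase from 5%, 10% or 15% in the control arm gives power 0.995, 0.972 and 0.938, in line with the stated 92% or higher. The planning figures are not in dispute.

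**3. Share of trials in dispute: MRI effect as designed, no clinical effect.** With power 0.90 for MRI, a two-sided 5% clinical test and independent end points:

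| Meaning of *not favored* | Formula | Share |
|---|---|---|
| not significantly better | 0.90 × 0.975 | 0.878 |
| estimate at or below zero | 0.90 × 0.50 | 0.450 |
| significantly worse | 0.90 × 0.025 | 0.0225 |

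At an assumed correlation of 0.5 between the test statistics, the first two become 0.875 and 0.416 (bivariate normal).

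**4. Both effects as designed.** With power 0.90 and 0.92, the chance of an MRI-only win is 0.90 × (1 − 0.92) = 0.072 if independent, and 0.052 at correlation 0.5.

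**5. Error rate in favour of angioplasty, no effect on either end point.** Under Rule 1 it is 1 − 0.975² = 0.049 if independent. If the clinical result always decides, it is 0.025. The false-positive rate therefore also depends on which rule governs.

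**The case against.** The strongest reply is that the paragraph can be read as a general rule with a narrow exception. Rule 1 already covers the case where the other end point is not significant, and expressly allows the win to be on MRI. If Rule 2 took over every such win, the mention of MRI in Rule 1 would be empty, and so would the later restatement. Rule 2 also uses a different word: a null result beside a positive one need not be a conflict, whereas results in opposite directions are one. Ranking the clinical end point first in a true conflict is a legitimate choice.

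This stands as a plausible reading, and it is why the matter is one of undefined terms and not of two rules that can never be reconciled. It does not settle the matter, because the parenthesis defines conflict by *not favored*, which a null clinical result satisfies, and the restated Rule 1 carries no exception for it. The analysis plan may define the terms, but the two published sentences would still need to agree with it.

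Two stronger inferences are not supported:

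- **That MRI can never establish superiority alone, so the chance of success is either 90% or 2.5%.** That holds only on the broadest reading, with no clinical effect at all. It is one end of the range.
- **That the plan defeats its own safeguard against failed masking.** The Discussion says that the MRI result would then keep its validity and leave the study partly useful. It does not say that MRI would then decide superiority.

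**Conclusion.** The point holds as a conflict on the literal wording, confined to one outcome: MRI significantly favours angioplasty and the clinical end point does not. A clinical-only win is a success under both rules.

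The size is a range. In RRMS, with the designed MRI effect and no clinical effect, the disputed share runs from about 88% through 42% to 45% down to about 2%, according to the meaning given to *not favored*. The 88% and 2% assume independent end points, and the middle range covers correlations from 0.5 to 0. If both effects are as designed, even the broadest reading touches only about 5% to 7% of trials. The article gives no MRI power for SPMS, so no share is computed there.

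The breadth of that range is itself the reason to act: the text leaves open whether the plan's best-powered route to success counts when it succeeds alone.

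**What to change.** Before unblinding, replace the two sentences with one rule and make the later restatement agree with it. For example:

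- A significant advantage on either primary end point supports superiority, unless the other primary end point is significantly worse with angioplasty. In that case the clinical result determines the conclusion.
- An MRI win with a merely non-significant clinical result counts as success, and is reported as an MRI effect without a demonstrated clinical effect.

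This keeps the priority of the clinical end point where results truly oppose each other, and needs no change to the design or the data. In the scenario of step 3, success would have probability 0.90 × 0.95 + 0.025 = 0.88.

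The cost is wording, and the loss of freedom to choose the interpretation later. The example rule does settle on the higher of the two error rates in step 5: 0.0494 − 0.025 × 0.025 = 0.049 in favour of angioplasty. Whether to correct for two primary end points is a separate question and would not be free. Under a Bonferroni split (an assumption; the article describes no correction between the two), the MRI power of 90% would fall to about Φ(1.960 + 1.282 − 2.241) = Φ(1.00) = 0.84.

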## Abbreviations

CCSVI: Chronic cerebrospinal venous insufficiency; CEC: Clinical endpoint commission; CRO: Contract research organization; CSA: Cross-sectional area; DCC: Data coordination center; ECD: Echo color doppler; e-CRF: Electronic case report form; GCP: Good clinical practice; IDMC: Independent data monitoring committee; IJV: Internal jugular vein; ITT: Intention to treat; PP: Per protocol; MRI: Magnetic resonance imaging; MS: Multiple sclerosis; RRMS: Relapsing remitting multiple sclerosis; SPMS: Secondary progressive multiple sclerosis; VV: Vertebral vein.

